#### Measures related to QOL

The primary outcome of older adult quality of life is measured using the Patient-Reported Outcomes Measurement Information System (PROMIS) Global Health scale, a 10-item subjective measure of general health [39]. It includes a 4-item global physical health scale (Cronbach’s α = 0.81), a 4-item global mental health scale (Cronbach’s α = 0.86), and 2 additional items - general health and satisfaction with social roles - that can each be scored as a single item. PROMIS scales were developed using item response theory and capture a greater range of the trait being measured, with greater precision, than other instruments.

#### Measures related to costs

To quantify the tradeoff between the hypothesized improvements in QOL that Elder Tree may produce versus the cost of providing Elder Tree, we will use incremental cost-effectiveness ratios (ICERs). An ICER is the ratio of the change in costs of an intervention (compared with an alternative) to the change in the effect(s) of the intervention. The primary ICER will be incremental cost per increased QALY. QALYs will be calculated using the approach outlined by Revicki, *et al*. [40].

We will collect data for two types of costs: intervention cost and healthcare utilization cost. Intervention cost will be estimated using a modified version of The Drug Abuse Treatment Cost Analysis Program (DATCAP) [41]. The DATCAP instrument was originally developed for addiction treatment programs [41]. It has been previously adapted to assess the cost of a quality improvement intervention for addiction treatment [42] and has been adapted for use in this study. We will track: (1) system development costs, including costs associated with programming Elder Tree; (2) research costs, which include salaries and fringe benefits for members of the research team to collect outcome measures; (3) set-up and implementation costs, including salaries (with fringe benefits) for county coordinators; and (4) operating costs, such as hardware (touchscreen laptops), monthly data plans, information technology (IT) costs for maintaining the system, and research staff time for monitoring system use. We will make set-up, implementation, and operating costs available because we anticipate that potential payers (governmental agencies, insurance companies, health systems) will be most interested in these costs.

Healthcare utilization will be collected via bi-annual patient surveys using a modified version of the medical services utilization form [43]. Participants will be asked about their visits to the emergency room and urgent care, hospitalizations, and use of assisted-living facilities and nursing homes. A 6-month recall period is used. Per-patient estimates use average cost per day/episode from the literature multiplied by self-reported healthcare use collected via the medical services utilization form [44-47].

Summing the costs of the intervention and healthcare utilization provides an estimate of total costs for each participant. Costs and effects will be measured at the individual patient/household level, which will allow us to generate cost-effectiveness acceptability curves to represent uncertainty in the ICERs between the intervention and control groups [48].

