## Methods/Design

### Study design and hypotheses

The study is a randomized longitudinal trial conducted by the Active Aging Resource Center (AARC). AARC is a consortium of university, state, and community partners headquartered at the Center for Health Enhancement Systems Studies at the University of Wisconsin- Madison, WI, USA (CHESS). CHESS develops ICTs to help patients and their families improve their health and well-being. Previous CHESS ICTs have been proven effective in numerous randomized trials for a variety of conditions, including alcohol use disorders [16], lung cancer [17,18], pediatric asthma [19], breast cancer [20], and HIV [21]. CHESS also develops process improvement strategies for healthcare systems.

Participants in the study - older adults and their informal caregivers - are randomized to an intervention group that uses their usual sources of information and communication and has access to Elder Tree from laptops and other devices, or to a control group in which participants use only their usual sources of information and communication. Participants in the Elder Tree group receive access to Elder Tree for 18 months and, if needed, a computer and Internet service. The computer is almost always a touchscreen laptop; two participants have been given large monitors because of vision problems. Participants who have their own desktop, laptop, tablet, or smartphone use their own devices. Participants’ use of other services and interventions is not controlled during the trial in either group.

The primary hypothesis is that older adults assigned to Elder Tree will, compared with a control group, have improved quality of life (QOL). Secondary hypotheses are that older adults assigned to Elder Tree will have, compared with those in the control group, improved independence, lower healthcare costs per Quality-Adjusted Life Year (QALY), less loneliness, fewer falls, improved medication management, and greater ease of transportation and driving, and that informal caregivers with access to Elder Tree will have improved caregiver appraisal (reduced burden, increased mastery of caregiving, and increased satisfaction with the older adult receiving care), and improved coping strategies compared with caregivers without Elder Tree. We also hypothesize that self-determination theory (SDT) will mediate Elder Tree effects.

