In addition to estimating healthcare costs in both groups, we will estimate the cost of delivering Elder Tree to determine what a governmental entity or other organization would pay to provide Elder Tree on a per-household basis.

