**Both older adults and informal caregivers**	
Inclusion criteria	• Understand the consent form, which is in English
Exclusion criteria	• Being unable to give informed consent
	• Being unable to use Elder Tree (for example, poor vision that prevents reading a computer screen)

We changed our recruitment criteria from our original plans based on results of a pilot test. Originally, we planned to recruit older adults who had had, in the last 12 months, three of the bulleted inclusion criteria shown in Table 2, but these criteria proved to be too restrictive (that is, to eliminate potential participants who would likely benefit from Elder Tree) and, according to the county coordinators who did the screening, so time-consuming to evaluate and invasive of subjects’ privacy that they drove away potential participants. We have settled on recruiting patients who have one or more of the inclusion criteria.

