### Recruitment

Each of the three regions in the study is served by an Aging and Disability Resource Center (ADRC). ADRCs are state funded, single- or multi-county agencies in Wisconsin that connect older people and people with disabilities to information, assistance, and counseling. A county coordinator works out of each local ADRC office to recruit potential participants for the study. The county coordinators raise awareness and interest among older adults by giving presentations about the study in neighborhood centers, churches, clubs, congregate eating facilities, and other places. The county coordinators explain the study and the eligibility criteria and ask attendees to provide their contact information. To encourage older adults to provide their names, the coordinators offer a drawing at the end of a presentation in which one of the slips of paper with contact information will be drawn to receive a $10 gift certificate to a local restaurant. Older adults and caregivers who contact an ADRC are also encouraged to participate.

Older adults who provide their contact information are called to confirm eligibility. If the older adult is eligible (and the informal caregiver, if the older adult names an informal caregiver who is also eligible), the county coordinator sends the baseline survey in the mail and sets up a time for a home visit. During the home visit, the county coordinator explains consent and obtains the completed consent form (see the forms in Additional files 2 and 3) and baseline survey from the older adult (and caregiver, if there is one). To date (31 March 2015), we have recruited 392 older adult participants to the study. We plan to recruit 450 participants. Figure 1 shows the flow of participants through the trial.

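### County-coordinator salaries are placed in the cost category offered to payers, although much of the coordinators' described work is trial work for both arms; without an activity split the per-household delivery cost would be overstated.

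*Protocol article*

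**What the plan says.** Measures related to costs (Protocol article) defines four categories of intervention cost: system development, research, set-up and implementation, and operating. Research cost is described as "research costs, which include salaries and fringe benefits for members of the research team to collect outcome measures". The third category is "set-up and implementation costs, including salaries (with fringe benefits) for county coordinators". The article then says which categories are meant for outside use: "We will make set-up, implementation, and operating costs available because we anticipate that potential payers" will be most interested in them. Study design and hypotheses gives the purpose, which is to "determine what a governmental entity or other organization would pay to provide Elder Tree on a per-household basis".

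The coordinators' work is described in other sections:

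- **Recruitment:** "A county coordinator works out of each local ADRC office to recruit potential participants for the study". They give presentations, and at a home visit they explain consent and collect the consent form and the baseline survey.
- **Participants, text below Table 2:** the eligibility criteria were changed partly because they took too long to evaluate, "according to the county coordinators who did the screening".
- **Randomization:** coordinators enrol participants without knowing the allocation sequence.
- **Intervention:** the coordinator is described as a grant-funded research-team member and makes a support call one week after the in-home training. Home set-up and training are assigned to the research team generally.

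**The concern.** The article separates research cost from set-up, implementation and operating cost so that a payer can see what delivery alone would cost. That works only if trial labour stays out of the payer-facing categories. Coordinator salaries are named in one of those categories without qualification, yet most of the coordinator tasks described exist because there is a trial. Leaving out the research category would not remove that labour.

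The per-household delivery cost is a stated aim, and cost per QALY is a secondary outcome. The error would run one way: Elder Tree households would carry the cost of recruiting, screening and consenting trial participants, controls included, and the system would look dearer than a payer would find it.

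**Working it through.** The article gives no cost, salary, hours or per-household price, so there is no figure to reproduce. The check sets the sections side by side and then does a simple apportionment.

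**Step 1. Classify the described tasks.**

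| Coordinator task | Section | Arms served | Nature |
|---|---|---|---|
| Presentations, recruitment | Recruitment | both | trial; part may also be needed in a roll-out |
| Eligibility screening | Participants; Recruitment | both | trial |
| Consent at home visit | Recruitment | both | trial |
| Enrolment, sequence unknown | Randomization | both | trial |
| Baseline survey collection | Recruitment; Table 3 | both | trial; outcome measurement |
| Call one week after training | Intervention | Elder Tree only | delivery |
| Home set-up and training | Intervention | Elder Tree only | delivery; done by the research team, which may include coordinators |

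**Step 2. Compare with the article's own categories.** Table 3 schedules the outcome measures at baseline, so collecting the baseline survey is outcome collection by a research-team member and fits the research category as defined. The same salary therefore fits two categories, and the article names it only under set-up and implementation.

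**Step 3. Size of the effect.** Inputs: 225 per group (Sample size), 1:1 allocation (Randomization). Let W be total coordinator salary and f the share of coordinator time that is delivery. The value of f is not in the documents.

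- Booked whole: W/225 per Elder Tree household.
- Delivery only: fW/225.
- Ratio: (W/225) / (fW/225) = 1/f.

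| f (assumed) | Overstatement of coordinator component |
|---|---|
| 1.00 | 1 (none) |
| 0.75 | 1.33-fold |
| 0.50 | 2-fold |
| 0.25 | 4-fold |

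**Step 4. Where the excess comes from.** With R trial hours per enrolled older adult and S delivery hours per Elder Tree household, the booked hours per Elder Tree household are (450R + 225S)/225 = 2R + S, against S for delivery. Of the excess 2R, one R is trial work on the household itself and the other R is trial work on a control.

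The factor applies to the coordinator component only. The whole per-household cost is inflated by less, because the other set-up and operating items are unaffected.

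**The case against.** The strongest reply is that the article does not say the whole salary goes into set-up and implementation, nor that it is divided over Elder Tree households alone. Costs come from a modified DATCAP that is not shown, and a condensed article may leave time apportionment to that instrument. The research category is also worded loosely enough to take coordinator time spent on baseline surveys. Coordinators may share in home set-up and training, and some outreach through the local resource centres could be a real roll-out cost. Each of these raises f or removes the error.

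Much of this stands, and it limits what can be claimed. It does not dispose of the point, because the article goes beyond leaving a detail open: it assigns these salaries to a category, and that assignment overlaps its own description of research cost. Even if baseline-survey time is read into the research category, recruitment, screening and consent are not named there.

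A reader might also infer that laptop and data-plan costs are averaged over homes that did and did not need them. The documents do not support this. Equipment is supplied only where needed, no averaging rule is stated, and costs are to be measured at the patient or household level. A mean over homes would in any case be correct for a payer with the same mix of device owners. Nor would an ICER by receipt of equipment be sound: receipt occurs only in the Elder Tree arm, whereas the randomization stratum is device ownership, so there would be no matching control group.

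**Conclusion.** The point holds as a risk of overstatement in one direction. If coordinator salaries are booked as the article words it, the per-household delivery cost includes trial labour, part of it spent on controls. The coordinator component is overstated by 1/f, with f unknown; the illustrative range is 1.33- to 4-fold for f from 0.75 to 0.25, with no error at f = 1 or if the cost instrument already apportions time.

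The effect on the ICER is conditional. The article adds intervention cost to healthcare utilization cost without saying which of the four categories enter, so the ICER is affected only if set-up and implementation cost is included and research cost is not.

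A reader might conclude that the payer price is wrong, or attach a dollar or per-QALY figure to the error. Neither is supported: the article states no price, and any such figure would rest wholly on assumed hours, wages and QALY gains. The primary quality-of-life analysis is not affected.

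**What to change.** In Measures related to costs, replace the single entry for coordinator salaries with a split by activity:

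- **Research cost:** screening, consent, baseline survey collection and all work on control households.
- **Set-up and implementation cost:** Elder Tree set-up and training where coordinators do it, the one-week call, and user support.
- **Separate line:** outreach that a payer would also need, so that it can be included or left out.

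State which categories enter the intervention cost used in the ICER. If the modified DATCAP already divides staff time in this way, one sentence saying so is enough.

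The cost is a time split on the cost form. The small downside is that 392 of the planned 450 older adults had been recruited by 31 March 2015, so hours already worked need a retrospective estimate, reported as a range.

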#### Measures related to caregivers and mediation

Two instruments will assess the results of using Elder Tree on caregivers. A combination of survey items and Elder Tree use data will assess the mediating effect of the three constructs of SDT. Computer-aided content analyses of discussion group posts will be used to explore the relationship between the reception and expression of emotional content and outcomes.

### Sample size

We originally targeted a sample size of N = 300 (150 per group), which would provide 80% power to detect an effect size of Cohen’s d = .4, assuming a response rate near 80% (similar to that of other CHESS studies [16]). Given our diffuse system, we made a decision to extend our focus to individuals and dyads that would benefit from one or two aspects of our system rather than multiple features, with a larger sample therefore needed to detect the greater range of incremental effects on discrete outcomes. More specifically, we set a revised target sample size of N = 450 (225 per group), which would provide 80% power to detect a smaller effect size of Cohen’s d = .3 with an 80% response rate.

### Timeline

Recruitment began in November 2013 and will end in May 2015. The intervention period will end in November 2016. Figure 2 shows the timeline and status of the trial.

**Figure 2 Fig2:**
[figure not shown]
Timeline.

### Data analysis

We will evaluate the effects of Elder Tree by comparing intervention and control participants at 6-, 12-, and 18-month assessments. We will use mixed-effects models to evaluate our primary and secondary hypotheses, where pretest score functions as a covariate, treatment condition is a between-subjects factor, and the multivariate outcome reflects scores for a given assessment across the 3 time points (months 6, 12, and 18). Separate analyses will be conducted for each outcome.

We will use path analysis to test whether the constructs of SDT mediate the relationship between Elder Tree and participants’ QOL at 6, 12, and 18 months. Mediation will be tested based on the significance and size of the specific indirect effects of system use through SDT constructs on relevant outcomes [49-51], as well as the overall fit of the model. Overall model fit will be assessed with statistics traditionally used for this task (for example, CFI, TLI, RMSEA).

Secondary analyses will lend further insight related to primary hypotheses’ findings. The intercorrelations between studied outcomes (for example, Instrumental Activities of Daily Living (IADLs), QOL) and mediator (SDT) will clarify whether these outcomes represent unique versus highly-correlated outcomes. Additional analysis will disaggregate overall Elder Tree effects into component services. Given the non-random selection of services and the potential correlation between the use of certain services, this analysis will address whether a service was used and the intensity of that use. This should reduce multi-collinearity issues in regression analysis and provide insights into each service’s contributions. Outcomes associated with specific Elder Tree services will also be compared between users and non-users of specific services in an exploratory Complier Average Causal Effect (CACE) analysis to examine whether actual use of a service (rather than randomized access to it) is associated with improved outcomes. We will also examine trends within groups over time (for example, whether gains from Elder Tree at 6 and 12 months are maintained to 18 months).

Because we anticipate that Elder Tree will take at least 3 months to have an effect, we plan to conduct exploratory analyses that mirror the aforementioned analyses but exclude participants who die or move to a nursing home or assisted living facility within the first 3 months of the intervention.

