### Randomization

The project statistician used a computer-generated allocation sequence to randomize eligible older adults (or older adult/caregiver dyads) in a 1:1 ratio to intervention (Elder Tree) or control. Randomization is stratified by geographic region, whether a participant has his or her own computer or other device, and living alone, using random blocks of 4 and 6. Randomization is implemented by the project director using sequentially numbered, sealed, opaque envelopes. The sequence is thus unknown to the county coordinators who enroll participants. Because of the nature of the intervention, neither participants nor research staff are blinded to allocation.

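### The stated mixed model names none of the three stratification factors; if these predict outcome beyond the pretest score, a little precision is forgone

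*Protocol article*

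**What the plan says.** The Randomization section of the protocol article states: "Randomization is stratified by geographic region, whether a participant has his or her own computer or other device, and living alone". Allocation is "in a 1:1 ratio to intervention (Elder Tree) or control", in random blocks of 4 and 6. Region has three levels (urban, suburban, rural) and the other two factors are yes/no, so full crossing gives 3 × 2 × 2 = 12 strata.

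The Data analysis section describes the mixed-effects model for the primary and secondary hypotheses as one "where pretest score functions as a covariate, treatment condition is a between-subjects factor", with the outcome measured at months 6, 12 and 18. The Abstract repeats this. Neither place names a stratification factor as a model term, and no part of the article says that the factors are excluded.

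The Sample size section plans 225 per group for "80% power to detect a smaller effect size of Cohen’s d = .3 with an 80% response rate". It credits no gain from any covariate.

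**The concern.** Stratified blocks keep the arms close to balanced within each stratum, so outcome differences between strata contribute little to the true sampling variance of the treatment effect. A model without stratum terms still counts those differences as residual variance. If they persist after adjustment for the pretest score, the model's standard error exceeds the true one, confidence intervals are wider than they need be, and the test rejects slightly less often than its nominal level.

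The factors could plausibly matter. Loneliness is a secondary outcome and living alone is a stratum. The regions differ in setting, and each has its own coordinator. Having one's own device decides whether an intervention participant is given a computer. What is at stake is precision on the primary outcome and the continuous secondary outcomes.

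**Working it through.** **Inputs from the article.** 225 per group, 80% response, d = 0.3, 80% power, 1:1 allocation, 12 strata, blocks of 4 and 6.

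**Assumptions.** Two-sided alpha of 0.05, which the article does not state. Also s, the share of variance remaining after pretest that the strata explain, for which the documents give no figure; 2%, 5% and 10% are shown.

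**The plan's own figure.** Evaluable per group: 2 × (1.96 + 0.8416)² / 0.3² = 174.4, so 175. Allowing for response: 175 / 0.8 = 218.75, so 219 per group and 438 in all, against 450 planned. With 225 × 0.8 = 180 evaluable per group, the noncentrality is 0.3 × √(180/2) = 2.846 and power is Φ(2.846 − 1.96) = 81.2%. The planned size therefore reproduces, with a small margin.

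**Effect of leaving the strata out.** Take d on the scale of the residual SD after pretest, and suppose that the blocks remove between-strata variance fully from the contrast. Then:

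- SE overstatement = 1/√(1 − s) − 1
- Type I error without strata = 2 × [1 − Φ(1.96/√(1 − s))]
- Power without strata = Φ((2.846 − 1.96)/√(1 − s))
- Power with strata = Φ(2.846/√(1 − s) − 1.96)

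| Assumed s | SE overstated by | Type I error without strata | Power without strata | Power with strata | Forgone (points) |
|---|---|---|---|---|---|
| 2% | 1.0% | 4.8% | 81.5% | 82.0% | 0.5 |
| 5% | 2.6% | 4.4% | 81.8% | 83.1% | 1.3 |
| 10% | 5.4% | 3.9% | 82.5% | 85.1% | 2.6 |

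**Check by simulation.** The design was simulated with 12 strata, blocks of 4 and 6, 450 randomized, 80% random response, an assumed pretest correlation of 0.6, one follow-up time and 4,000 runs per setting.

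| Assumed s | Type I error without strata | Power without strata | Power with strata |
|---|---|---|---|
| 2% | 5.0% | 80.7% | 81.3% |
| 5% | 4.8% | 80.3% | 81.2% |
| 10% | 4.0% | 81.3% | 84.5% |
| 20% | 3.5% | 81.8% | 87.9% |

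With the strata in the model, simulated type I error was 5.0% to 5.2%. The simulation error of a rate near 5% is √(0.05 × 0.95/4000) = 0.34 points, so no conservatism is discernible at 2% or 5%. It shows at 10% and above. Random non-response undoes part of the within-stratum balance, so the formulas, which assume full balance, somewhat overstate the conservatism.

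**If d = 0.3 is on the raw SD scale.** With an assumed pretest correlation of 0.5, the noncentrality is 2.846/√0.75 = 3.286 and power without strata terms is already about 90.8%. The same formulas then give a forgone gain of about 0.3, 0.8 and 1.5 points at s = 2%, 5% and 10%.

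**The case against.** The strongest objection is that a one-sentence model description in a journal article is not a closed covariate list. It also gives no covariance structure and no link for counts or binary items, and the Abstract only repeats it. A reader might infer that the trial will certainly analyse its data without the strata. The article does not support that, since an analysis plan not shown here may add them. What remains is that the article names one covariate and leaves out the factors it randomized by, so anyone following it as written would fit the model without them.

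A second objection is that the pretest score, measured on the same instrument, should absorb much of any stable difference between strata. This stands. That living alone relates to loneliness does not show that it predicts loneliness given baseline loneliness. The harm is therefore conditional, and no residual R² is documented.

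A reader might also infer that the trial is underpowered or its test invalid. Neither follows. The sample size relies on no covariate, 180 per arm gives 81.2% at d = 0.3, and any error in the type I rate is on the conservative side.

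Finally, the standard-error formula is for linear models. It should not be carried over to fall counts or binary medication items. Nor does the point reach the cost-effectiveness analysis, where the article describes incremental ratios and acceptability curves and no regression.

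**Conclusion.** The point holds as a conditional and modest inefficiency. The design stratifies on three factors and the stated model names none of them. If they explain 2% to 10% of the variance left after pretest, the overstatement of the standard error runs from about 1% to about 5%. The power forgone runs from about 0.5 to 2.6 points with d on the residual scale, and less if d is on the raw scale. Up to about 5% the effect is negligible in practice; it becomes material only if the strata are strongly prognostic beyond pretest. This is precision given up, with no shortfall against the planned 80%, no inflation of type I error and no bias in the estimate. The size rests on the assumed residual R² and a two-sided alpha of 0.05.

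**What to change.** In the Data analysis section, add region (three levels), own device (yes/no) and living alone (yes/no), as recorded at randomization, as fixed effects in the mixed models for the primary outcome and the continuous secondary outcomes. For count and binary outcomes, prespecify the same covariates and note that an odds ratio then becomes conditional on them. If an existing analysis plan already includes the factors, the article's description need only be brought into line with it.

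The cost is one sentence and 2 + 1 + 1 = 4 degrees of freedom, against about 360 evaluable older adults. No new data are needed, because all three factors are known at randomization. Four main effects will not remove any variance due to interactions among the strata, so the gains shown are upper figures to that extent. The terms should be fixed before outcomes are analysed, so that the choice cannot depend on the results.
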